## Abstract

**Introduction**: Mental disorders, particularly depression and anxiety, represent a leading source of morbidity and disability in young adults, a group increasingly exposed to cumulative psychological processes and environmental stressors. Although evidence links healthy dietary patterns with improved mental health symptoms, the specific contribution of nut consumption (rich in anti-inflammatory, antioxidant, and neuroprotective compounds) remains insufficiently examined in this population. Current evidence also lacks robust data on the dose–response effects of nut consumption and mechanistic pathways involving biomarkers relevant to brain function and mental health. The Nuts4Brain-RCT will investigate the impact of a 6-month mixed-nut consumption intervention on mental health symptoms, cognitive functioning, sleep quality, overall well-being, health-related quality of life, and biochemical brain function mediators in young adults. **Methods and analysis**: A 6-month, randomized, single-blinded, three-arm, dose–response, parallel-group clinical trial will be conducted with 135 university students aged 18–24 years from the University of Castilla-La Mancha, Cuenca, Spain. The participants will be randomly assigned in a 1:1:1 ratio to one of three groups: (1) a control group maintaining their habitual diet while avoiding nut consumption; (2) a 30 g/day mixed-nut consumption group; or (3) a 60 g/day mixed-nut consumption group. The nut consumption intervention will include unsalted, unroasted walnuts, almonds, hazelnuts, and pistachios. The primary outcomes will include depressive (BDI-II) and anxiety (GAD-7) symptoms, perceived stress (PSS-10), cognitive performance (NIH Toolbox), and plasma brain-derived neurotrophic factor (BDNF). Assessments will take place at baseline and at 3 (intermediate), 6 (end of intervention) and 12 months (follow-up). Repeated-measures mixed-effects models will be applied to estimate the effects of nut consumption and dosage on mental health outcomes. **Ethics and dissemination**: The study adheres to the principles of the Declaration of Helsinki and the Singapore Statement on Research Integrity and obtained approval from the Clinical Research Ethics Committee of the Virgen de la Luz Hospital, Cuenca, Spain (REG: 2025/E0125). The findings will be disseminated through high-impact open-access peer-reviewed publications, presentations at scientific conferences, and social media platforms. **Trial registration**: ClinicalTrials.gov. **Identifier**: NCT07292610.

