### 2.4. Sample Size Calculation

The sample size was calculated using the Grayling and Wason method for multi-arm trials [56], which is appropriate for a design with two experimental groups and one control group. A medium effect size (Cohen’s d = 0.5) and homogeneity of variance (σ = 1) were assumed across groups as recommended [57] when no clear estimate on this association is provided in the available studies with similar design [48,49]. With a two-sided α of 0.05 and 80% power (β = 0.20), the required sample size was obtained via the “des_ss_norm()” function in R statistical software, version 4.5.2 (R Core Team, 2024, Vienna, Austria). All three arms were allocated at a 1:1:1 ratio. To account for multiple comparisons, the Benjamini–Hochberg correction was applied to control the false discovery rate. The power calculation was based on a disjunctive criterion, which estimates the probability of detecting at least one significant difference between any intervention group and the control group. The initial calculation yielded a requirement of 42 participants per group. After accounting for an anticipated 20% dropout rate, the final sample size was adjusted to 53 participants per group. This resulted in a total target enrollment of 159 participants across all three study arms. The participants will initially be drawn from the 463 students enrolled in the Nuts4Brain-Z observational study (data collection September–December 2023) [58,59,60]. If necessary, recruitment will be extended to additional UCLM undergraduate students to reach the target sample size.

The sample size calculation was based exclusively on the primary outcome as we did not find previous studies examining the association between nut consumption and our secondary outcomes that would provide the necessary effect size estimates for power and sample size calculations. Consequently, the study should be considered exploratory with regard to these secondary outcomes, and any findings related to them should be interpreted with appropriate caution. While our sample size provides adequate power for detecting changes in the primary outcome, we acknowledge that it may be underpowered for detecting meaningful differences in secondary outcomes, particularly if the true effects are small to moderate in magnitude.

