### 2.12. Limitations and Contingency Plan

#### 2.12.1. Limitations

The study uses a single-blind design because participants cannot be blinded to nut consumption. This may introduce expectancy bias, but it is mitigated by blinding outcome researchers. Primary mental health outcomes rely on self-report questionnaires and are therefore subject to reporting biases. However, validated instruments and complementary objective measures, such as cognitive tests and biomarkers, are included. Adherence cannot be directly observed in free-living conditions. Monitoring through biweekly contact and determination of vitamin E blood concentrations at each visit improves, but does not guarantee, compliance and does not prevent contamination of the control group. The sample consists of university students aged 18–24 years from a single campus. This limits generalizability but enhances internal validity in an understudied population. The study may be underpowered for small effects, secondary outcomes, or subgroup analyses, particularly if dropout exceeds the anticipated 20%. Finally, the 6-month intervention and follow-up period may be insufficient to assess long-term or delayed effects.

The extensive assessment protocol may increase participant burden and the risk of attrition. Although a validated FFQ will be used, dietary assessment remains imprecise and is subject to underreporting and recall bias. Additionally, some control group participants may live with participants from other study groups, which makes complete prevention of contamination unrealistic. While the CG will be instructed to avoid nuts from any source and the IG-30 and IG-60 groups will be instructed to avoid nuts from non-study sources, accidental or intentional nut consumption may still occur.

Finally, academic stressors (e.g., exams, tight assignment deadlines) and seasonal variations may affect mental health and thereby influence the study associations.

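### Planned enrolment is 135 in the abstract but 159 in section 2.4; with 135, the planned 20% dropout leaves 36 per arm against the 42 required

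*Protocol article*

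**What the plan says.** The abstract states that a three-arm "parallel-group clinical trial will be conducted with 135 university students", randomised 1:1:1.

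Section 2.4 (Sample Size Calculation) builds a different total in three steps:

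- The base requirement: "The initial calculation yielded a requirement of 42 participants per group".
- An allowance for 20% dropout, which raises 42 to 53 in each arm.
- The sum over the three arms: "This resulted in a total target enrollment of 159 participants across all three study arms".

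The same section confirms equal allocation: "All three arms were allocated at a 1:1:1 ratio". It sets the planning assumptions as d = 0.5, SD = 1, two-sided alpha of 0.05, 80% power, Benjamini–Hochberg correction, and a disjunctive criterion (at least one nut arm differs from control). Section 2.12.1 (Limitations) uses the 20% dropout figure again when it warns that the study may be underpowered.

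**The concern.** Both totals stand in the current text and describe the same planned enrolment, yet they differ by 24 participants. Nothing labels 135 as a completer count, a minimum or a superseded figure.

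The number has work to do. Section 2.4 extends recruitment beyond the initial pool of 463 students if that is needed to reach the target, and section 2.12.2 (Contingency Plan) triggers extra recruitment when enrolment targets are missed. Both provisions need a single target. If the trial closed at 135, a reader could not tell whether that was the plan or a shortfall. The planned dropout would also take the trial below the per-arm number on which its power statement rests.

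**Working it through.** **Inputs.** From section 2.4: 42 evaluable per arm, 20% dropout, three equal arms, d = 0.5, SD = 1, alpha 0.05, Benjamini–Hochberg over two comparisons with control, disjunctive power of 80%. From the abstract: 135 in total.

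**1. Reproduce the 159.** Inflation: n / (1 − dropout) = 42 / 0.80 = 52.5, rounded up to 53. Total: 3 × 53 = 159. Check: 53 × 0.80 = 42.4, so 42 completers per arm remain. Section 2.4 is internally consistent.

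**2. Try to reproduce the 135.**

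| Candidate | Calculation | Total |
|---|---|---|
| Evaluable total | 3 × 42 | 126 |
| Completers from 159 | 159 × 0.80 | about 127 |
| Inflation by multiplying | 42 × 1.2 = 50.4, up to 51; 3 × 51 | 153 |
| Requirement of 36 per arm | 36 / 0.80 = 45; 3 × 45 | 135 |

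Only the last row gives 135, and the article states no requirement of 36 per arm.

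**3. Apply the planned dropout to 135.** 135 / 3 = 45 per arm; 45 × 0.80 = 36 completers per arm, 108 in total. Shortfall: 42 − 36 = 6, and 6 / 42 = 14%. The dropout at which 42 per arm would remain is 1 − 42/45 = 6.7%, a third of the planned rate.

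**4. Power at 36 and 42 per arm.** Let Z1 and Z2 be the two comparisons with control. Treat them as bivariate normal with common mean d × √(n/2), assuming both nut arms have d = 0.5, and with correlation 0.5 from the shared control. With a per-tail level a, Benjamini–Hochberg rejects at least once if either Z exceeds the critical value at a/2, or if both exceed the critical value at a. Integrating over that region gives:

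| Per arm | 0.05 one-sided | 0.05 two-sided |
|---|---|---|
| 36 | 74.5% | 63.2% |
| 42 | 80.2% | 70.0% |
| 45 | 82.6% | 73.1% |
| 53 | 87.8% | 79.95% |

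The smallest n that reaches 80% is 42 in the one-sided column, which matches section 2.4, and 54 in the two-sided column. Within either column, moving from 42 to 36 costs about 6 to 7 points (80.2 − 74.5 = 5.7; 70.0 − 63.2 = 6.8).

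**The case against.** The contradiction itself cannot be argued away, but four points limit what follows from it.

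- **Section 2.4 is the operative section.** It derives the number and calls it the target, and no text makes the abstract figure a stopping rule. The 135 may simply be an uncorrected leftover. This is plausible, but the article does not say so, and a leftover total still needs correcting.
- **The 63.2% must be read against 70.0%, not 80%.** About 10 points of the gap to 80% come from the sidedness: the base of 42 reproduces only with 0.05 one-sided, although the text says two-sided. That mismatch exists equally at 159. This is right, and it is why the two columns above are kept apart.
- **Restoring 159 does not secure 80% power on a two-sided 0.05.** That would need 54 evaluable per arm, hence 54 / 0.80 = 67.5, rounded up to 68 per arm and 204 in total. This also stands, but it is a separate matter and it makes 135 look worse.
- **36 is not the number analysed.** The primary analysis is intention-to-treat with multiple imputation or mixed models, so participants who leave after month 3 still contribute. This is fair: the effective number lies somewhere between 36 and 45 per arm, with power on the one-sided basis between 74.5% and 82.6%. The same allowance applied to 159 gives 80.2% to 87.8%. The article's own inflation from 42 to 53 counts completers, so the comparison of 36 with 42 is on its own planning terms.

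None of these points reconciles the two totals.

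**Conclusion.** The concern holds. The article states two incompatible enrolment totals, and only 159 follows from its stated inputs. At 135 the trial would fall 6 per arm (14%) short of its own requirement under its own 20% dropout. It would lose about 6 to 7 points of disjunctive power, from 80.2% to 74.5% on the basis that reproduces 42.

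The enrolment arithmetic is exact given 1:1:1 allocation and 20% dropout. The power figures rest on a normal approximation, both nut arms at d = 0.5, and a count of completers only. The 42 is taken as the article's stated requirement; it is not confirmed for a two-sided 0.05.

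Total enrolment is a core design figure, so this must be corrected.

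**What to change.** Choose one target and state it everywhere.

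- If section 2.4 is the plan, change 135 to 159 in the abstract. Check Figure 1, which is not reproduced in the text available, for the same figure.
- If 135 is the plan, rewrite section 2.4 to 45 per arm. State that 20% dropout leaves 36, give the resulting power on the alpha basis actually used, and amend the statements in section 2.4 and the Discussion that the sample is adequate for the primary outcome and for medium effects.

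The first option costs one corrected number and the second one restated calculation. The article says it was written before recruitment and data collection, so either can be done before the target is used.

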### 2.5. Participant Recruitment

Following ethics approval, authorization will be obtained from university authorities at UCLM in Cuenca, Spain. Professors will be contacted to request 15 min of class time for a brief presentation about the study, during which flyers will be distributed. Interested students can provide contact information either by giving their mobile number or scanning a QR code to complete an online form. QR codes will also be available on posters throughout the university. A research team member will then contact interested students via WhatsApp LLC (Meta Way, CA, USA) to answer questions and, if they agree to participate, schedule the baseline visit. All participants will be instructed to avoid nut consumption for at least 7 days before the baseline assessment.

### 2.6. Randomization and Allocation Processes

The randomization and allocation processes will occur before the baseline assessment. To ensure balance across study arms, randomization will be stratified by sex considering the ratio of 2 males:3 females, since this is the ratio observed in the reference population of university students on the campus of Cuenca of the UCLM. Allocation concealment will be maintained using sequentially numbered, opaque, sealed envelopes, which will be opened only at the point of assignment. To minimize selection bias, the allocation sequence will remain concealed from the research team until the end of the intervention (six months). Participants will be informed of their group allocation immediately after the randomization procedure has been completed.

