The intention-to-treat (ITT) analysis will serve as the primary analysis to preserve randomization benefits and provide a conservative estimate of treatment effects, whereas the per-protocol (PP) analysis will serve as a sensitivity analysis to assess efficacy under optimal adherence conditions. The ITT analysis will include all randomized participants in their assigned groups regardless of adherence, with missing data handled using multiple imputation or mixed-effects models that accommodate incomplete observations. The PP analysis will include only participants who completed the intervention according to protocol specifications, with adherence thresholds defined a priori (e.g., self-reported consumption of at least 80% of nut doses assigned, and 5–15% increased blood concentrations of α-tocopherol) [61].

The interpretation of clinical significance will be based on established minimal clinically important differences (MCID) for each outcome measure. For example, for the BDI-II, we will apply a 17.5% reduction as determined by Button et al. (2015) [100], who found that this represents the threshold at which patients report feeling “better” based on anchor-based methods. We will also evaluate whether participants transition between established severity categories (minimal: 0–13; mild: 14–19; moderate: 20–28; severe: 29–63) [63]. For the GAD-7, we will use the 4-point MCID threshold established by Toussaint et al. (2020) [101] to assess whether participants cross the clinical cut-off of ≥10 points, indicating clinically significant anxiety [66]. Given the lack of consensus on the MCID for the PSS-10, we will interpret effect sizes of Cohen’s d ≥ 0.5 as clinically relevant [57] and contextualize changes using reference values for the target population [102]. We recognize that in preventive nutritional interventions targeting non-clinical populations, small but consistent effects may have beneficial public health impacts [103], particularly given that dietary modifications represent accessible and low-risk interventions.

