Limitations include the inability to blind participants due to the whole-food nature of the intervention, which may introduce performance or expectation bias. To minimize these biases, a multi-layer strategy will be implemented. First, allocation will be strictly concealed using opaque, sealed envelopes until baseline assessments are completed. Following randomization, outcome assessors and data analysts will remain blinded to group allocation throughout the trial. During the intervention period, compliance will be monitored via blood vitamin E concentrations. At assessment points, self-reported mental health measures (BDI-II, GAD-7) will be complemented with objective cognitive assessments (NIH Toolbox) and biological markers (BDNF, inflammatory markers, cortisol). Together, these measures help mitigate expectancy effects and strengthen the trial’s internal validity. The recruitment of university students enhances sample homogeneity but may also restrict the generalizability of the findings to broader young adult populations. Finally, although the study is powered to detect medium effect sizes, mental health outcomes are multifactorial and may be influenced by unmeasured genetic or environmental factors.

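### Section 2.6 and the Discussion give opposite orders for allocation disclosure and baseline; followed as written, section 2.6 would make the self-reported baselines post-disclosure measures

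*Protocol article*

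**What the plan says.** Section 2.6 (Randomization and Allocation Processes) fixes the order: "The randomization and allocation processes will occur before the baseline assessment". It ends: "Participants will be informed of their group allocation immediately after the randomization procedure has been completed". Read together, participants know their arm when they attend visit 1.

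The Discussion (section 3), listing measures against performance and expectation bias, puts first that "allocation will be strictly concealed using opaque, sealed envelopes until baseline assessments are completed".

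On who is blinded, section 2.12.1 says: "The study uses a single-blind design because participants cannot be blinded to nut consumption". The Discussion says that "outcome assessors and data analysts will remain blinded to group allocation throughout the trial". Section 2.6 keeps the allocation sequence from the research team only to the end of the six-month intervention.

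On the analysis set, section 2.11 says: "The ITT analysis will include all randomized participants in their assigned groups regardless of adherence".

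**The concern.** BDI-II, GAD-7 and PSS-10 are primary outcomes and tablet self-reports (sections 2.10.1 and Table 1). Section 2.12.1 concedes that they are open to reporting bias, but it does not say that this bias could reach baseline. Under section 2.6, visit 1 is answered by students who already know whether they will receive free nuts or must avoid them.

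Much of the plan leans on visit 1: the repeated-measures model, the check for baseline differences, moderation by baseline mental health (section 2.11), and the 17.5% BDI-II reduction used for clinical interpretation. If baseline follows disclosure, none of these has a reference value untouched by knowledge of the arm, and no later analysis can recover one.

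Disclosure before visit 1 also opens a gap in which a student can withdraw because of the arm assigned. That student has been randomised but has contributed no measurement.

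**Working it through.** The article states no figure on this point, so the check is mainly a comparison of texts.

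| Place | Order or instruction |
|---|---|
| Section 2.5 | Baseline visit is scheduled once a student agrees to take part; all participants avoid nuts for at least 7 days beforehand; no randomisation step is mentioned |
| Section 2.6 | Randomise, disclose the arm, then baseline |
| Section 2.7 | Arm-specific instructions begin once randomisation is complete |
| Section 2.10 | All study variables are collected at visit 1 and repeated at later visits |
| Section 3 | Baseline completed, then allocation revealed |

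1. Sections 2.6 and 3 give opposite orders. Figure 1 is not shown, and no other readable text decides between them.
2. Under section 2.6, a nut-arm participant could receive instructions to eat nuts while still within the common 7-day avoidance period of section 2.5. Under the order in section 3 this tension does not arise.
3. A participant who leaves between disclosure and visit 1 has no outcome record. A mixed model fitted to observed outcomes gains nothing from that participant. Multiple imputation could use the arm, sex (the stratification factor) and whatever recruitment data exist. The 20% dropout allowance in section 2.4 is not split by timing, so the number affected is unknown.

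**Scale, under assumed values.** Let s be the between-arm difference (nut arm minus control) in how far knowing the arm moves the mean reported baseline, in SD units. Let ρ be the correlation between baseline and follow-up. The documents give neither. Take σ = 1 and the planned d = 0.5 from section 2.4, and suppose the true follow-up scores are unaffected by s.

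- Change-from-baseline contrast: bias = −s. For s = 0.1 the size is 0.10 SD, and 0.10/0.5 = 20% of d. For s = 0.2 it is 0.20 SD, and 0.20/0.5 = 40% of d.
- Baseline-adjusted contrast: bias = −ρs. With ρ = 0.5 the size is 0.5 × 0.1 = 0.05 SD to 0.5 × 0.2 = 0.10 SD. With ρ from 0.3 to 0.7 it runs from 0.3 × 0.1 = 0.03 SD to 0.7 × 0.2 = 0.14 SD.
- Two-sided 5% type I error of the adjusted contrast with 42 per arm (section 2.4) and ρ = 0.5: the standard error is √[(2/42)(1 − 0.25)] = 0.189. The bias is then 0.05/0.189 = 0.26 to 0.10/0.189 = 0.53 standard errors, which gives about 5.8% to 8.3%. Over ρ from 0.3 to 0.7 the range is 5.2% to 14.6%.

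The sign depends on s. If knowing the arm lowers reported symptoms in the nut arms at baseline, a change score understates benefit. If it raises them relative to control, benefit is overstated.

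**The case against.** The strongest reply is that section 2.6 may simply be a drafting slip. Section 2.5 moves from agreement to the baseline visit with no randomisation step and gives everyone the same nut-avoidance instruction, which fits the Discussion better. This stands to the extent that a reader who infers that baseline will certainly be collected unblinded goes too far: that follows only if section 2.6 is the operative text. The contradiction remains, however, and section 2.6 is the methods section that staff would follow.

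A reader might also infer a second flat contradiction, between concealment that ends at six months and blinding throughout the trial. The documents do not support that. Section 2.6 speaks of the sequence and the research team, whereas the Discussion speaks of assessors and analysts. Section 2.2 calls this a 6-month trial, and section 2.7 uses the full duration of the trial for the period in which nuts are supplied. What stands is that blinding at the 12-month visit is unclear.

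A third tempting reading is that the intention-to-treat set could not be analysed. Sections 2.11 and 2.12.2 provide for multiple imputation, so it could be, though weakly for anyone without visit 1 data. Withdrawal out of dislike for an arm is a possibility to which no document gives a rate.

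Finally, the bias figures rest on assumption. Questionnaire recall windows (two weeks for BDI-II and GAD-7, a month for PSS-10, a year for the food frequency questionnaire) reach back before disclosure if it falls close to the visit. Blood markers are unlikely to move merely because the arm is known. This limits the reach of the problem without removing it for the self-reports.

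**Conclusion.** The point holds as an internal contradiction with a conditional consequence. Sections 2.6 and 3 cannot both describe the conduct of the trial. If section 2.6 is followed, the baselines of the self-reported primary outcomes and the diet questionnaires become post-disclosure measures, and early withdrawals enter the intention-to-treat set without data.

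The size and direction of any bias are unknown. The 0.1 to 0.2 SD illustration shows only that a modest differential shift would not be negligible beside d = 0.5; the 20% to 40% should not be read as an estimate for this trial. The case for correction rests on the conflicting text and on the fact that a lost pre-disclosure baseline cannot be recovered. The Introduction says the article precedes recruitment and data collection, so it should be settled before the first participant is randomised.

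Blinding at 12 months is a secondary matter that needs clarifying and is not a firm contradiction.

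**What to change.** Rewrite section 2.6 so that the sealed envelope is opened, and the arm disclosed, only after all visit 1 assessments (blood sampling, questionnaires, cognitive and physical tests) are complete. This matches the Discussion and removes the tension between sections 2.5 and 2.7. Check that Figure 1 shows the same order.

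As a clarification, state that outcome assessors remain blinded through the 12-month visit, and that analysts work with coded arms if an analysis is done at six months.

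The cost is a wording amendment, with the prior ethics approval that section 2.12.2 requires. No visit or staff are added. Section 2.7 already has a researcher outside the clinical assessments hand over the nuts, and that person could open the envelope at the end of visit 1.

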### 2.7. Intervention Implementation

Once randomization is complete, participants will receive printed and verbal standardized instructions to maintain their usual lifestyle habits throughout the study period, except for nut consumption, where the following group-specific instructions will be provided:Control group (CG): Participants will be instructed to continue their habitual diet while avoiding direct nut consumption, although the sporadic consumption of foods that may contain trace amounts of nuts as ingredients (e.g., baked goods, ice cream) does not constitute a protocol violation.Intervention groups (IG-30 and IG-60): Participants will be instructed to consume 30 g or 60 g of unsalted, unroasted mixed nuts daily and to exclusively consume the amount of nuts provided by the researchers, refraining from consuming other sources of nuts. For the participants in the CG, sporadic exposure to trace amounts of nuts in processed foods (e.g., baked goods, ice cream) will be acceptable.

The nuts (a mixture of almonds, walnuts, pistachios, and hazelnuts) will be provided free of charge, in daily portions, to participants in the intervention groups for the full duration of the trial. The participants will be asked to incorporate nuts into their usual diet and to consume them in any uncooked manner they prefer, such as alone (only nuts), with salad, or yogurt.

At months 2 and 4, participants will be instructed to collect the prepacked bags containing the daily portions of nuts required for each intervention group during the subsequent period (i.e., participants in IG-30 will receive 30 g bags, and those in IG-60 will receive 60 g bags). To maintain a single-blind design, the nuts will be provided in person for each participant by a researcher who is not involved in clinical assessments. The bags containing the daily content of nuts will be specifically produced for the trial in accordance with established quality standards and sealed under a protective atmosphere. Each bag will contain a fixed mixture of nuts in the following proportions: 35% almond, 35% walnut, 20% unshelled pistachios, and 10% hazelnut. These nut mix proportions are based on the most consumed nut types in Spain and were designed to provide a balanced profile of fatty acids, micronutrients, and bioactive compounds while reflecting habitual intake, improving palatability and adherence, and facilitating translation into practical dietary recommendations.

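### Section 2.6 randomises and discloses the arm before baseline, while the Discussion says allocation stays concealed until baseline is done; if 2.6 is followed, the self-rated baseline scores are not clean pre-allocation values.

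*Protocol article*

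**What the plan says.** Section 2.6 sets the order in the Methods: "The randomization and allocation processes will occur before the baseline assessment". It adds that "Participants will be informed of their group allocation immediately after the randomization procedure has been completed", and that allocation uses "sequentially numbered, opaque, sealed envelopes, which will be opened only at the point of assignment". Section 2.7 continues from there: "Once randomization is complete, participants will receive printed and verbal standardized instructions", including the instructions specific to each arm.

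The Discussion (section 3) gives a different order. In its list of measures against performance and expectation bias, the first is that "allocation will be strictly concealed using opaque, sealed envelopes until baseline assessments are completed".

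Section 2.12.1 accepts that participants are not blinded ("The study uses a single-blind design because participants cannot be blinded to nut consumption") and that "Primary mental health outcomes rely on self-report questionnaires and are therefore subject to reporting biases". It does not say that the baseline scores themselves might be collected after disclosure. Section 2.10 applies the same measurement battery at visit 1 and at the later visits, and section 2.11 defines the intention-to-treat set as everyone randomised.

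**The concern.** In an open-label trial with self-rated primary outcomes, the baseline score is the one measurement that can be kept free of knowledge of the arm. If the arm is disclosed first, a reaction to the assignment can enter the baseline. Controls asked to give up nuts, for example, may rate themselves differently from participants offered a free supply. Blinded assessors give no protection here, because these scales are self-reported on a tablet (Table 1).

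Several planned analyses use the baseline as a pre-treatment reference. They are the repeated-measures model and the moderation by baseline mental health status (both section 2.11), and the interpretation thresholds in the same section, namely a percentage reduction in BDI-II and a 4-point change in GAD-7. A model that assumes equal baseline means across arms relies on randomisation to justify that assumption, and the justification is lost if baseline follows disclosure.

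There is a second, conditional risk. If disclosure precedes visit 1 by some days, a participant unhappy with the assignment may not attend. That person is in the intention-to-treat set with no data at all, and such losses may differ by arm.

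**Working it through.** **Step 1: order of events.** No figure in the plan is in dispute, so the passages are set side by side.

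| Event | Sections 2.6 and 2.7 | Section 3 (Discussion) |
|---|---|---|
| Randomisation and allocation | before baseline | concealed until baseline is complete |
| Envelope opened | at the point of assignment | by implication, after baseline |
| Participant told the arm | immediately after randomisation | by implication, after baseline |
| Arm-specific instructions | once randomisation is complete | not stated |

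The Discussion speaks of concealment rather than of when randomisation happens. But section 2.6 says the envelopes are opened only at assignment, so sealed envelopes until the end of baseline place assignment after baseline. That reverses section 2.6.

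**Step 2: illustration of the consequence if section 2.6 is followed.** Inputs:
- From the plan (section 2.4): n = 42 per arm, SD = 1, two-sided α = 0.05.
- Assumed, because the article gives neither: disclosure shifts the baseline difference between a nut arm and control by b = 0.1-0.2 SD, and the baseline to follow-up correlation is ρ = 0.5-0.7.
- Also assumed: the shift affects the baseline score only, there is no true effect, and the normal approximation applies.

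Formulas:
- Unadjusted standard error: √(2/42) = 0.218.
- Baseline-adjusted contrast: absolute bias = ρ × b; SE = 0.218 × √(1 − ρ²).
- Change score: absolute bias = b; SE = 0.218 × √(2(1 − ρ)).
- Rejection probability: Φ(−1.96 + bias/SE) + Φ(−1.96 − bias/SE).

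| b | ρ | Adjusted: bias | Adjusted: type I error | Change score: bias | Change score: type I error |
|---|---|---|---|---|---|
| 0.1 | 0.5 | 0.05 | 5.8% | 0.10 | 7.4% |
| 0.1 | 0.7 | 0.07 | 7.3% | 0.10 | 9.1% |
| 0.2 | 0.5 | 0.10 | 8.3% | 0.20 | 15.0% |
| 0.2 | 0.7 | 0.14 | 14.6% | 0.20 | 21.9% |

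Relative to the planned d = 0.5, the adjusted bias is 0.05/0.5 = 10% to 0.14/0.5 = 28%, and the change-score bias is 0.1/0.5 = 20% to 0.2/0.5 = 40%.

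The rejection formula is unchanged when the sign of the bias is reversed, so two-sided type I error rises for a shift in either direction. What depends on direction is whether a true effect is understated or overstated.

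**Step 3: the same calculation with baseline before disclosure.** Then b = 0 by design, both bias terms are zero and the rejection rate returns to 5%.

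**The case against.** The strongest reply is that this is a conflict of text, not a proven flaw in conduct. If the Discussion describes what will be done, the baseline is clean and one sentence in section 2.6 is wrong. Figure 1, which might show the order, is not reproduced in the text at hand. This stands. A reader might infer that section 2.6 is bound to govern and that every baseline score will be taken with the arm known, but the article does not settle that.

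The size of any shift is also unsupported. BDI-II and GAD-7 look back two weeks and PSS-10 one month (section 2.10.1), so if disclosure comes shortly before visit 1, most of the recall window precedes it. Section 2.11 names a repeated-measures mixed model without fixing how baseline enters, so neither bias formula is the plan's own analysis. A comparison of follow-up scores alone would not carry the baseline shift. These points limit the illustration but do not remove the contradiction.

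Early differential loss needs a gap between disclosure and visit 1. Section 2.5 describes only the baseline appointment, so randomisation could fall earlier on the same day. The loss is therefore a conditional risk.

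Three further inferences are tempting but not supported:
- **A clash with the nut-free week.** Section 2.5 says "All participants will be instructed to avoid nut consumption for at least 7 days before the baseline assessment", and section 2.7 gives arm instructions after randomisation. The article does not date the start of intake or the first supply, so early instructions for later intake are compatible with that week.
- **Ineligible people found only after randomisation.** Section 2.3 ties the pregnancy exclusion to the time of randomisation, which implies a check by then, and an article may leave the screening procedure to the full protocol.
- **A definite loss of power.** The direction of any shift is unknown, and section 2.4 plans disjunctive power without a baseline correlation, so no power loss can be read off the plan.

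**Conclusion.** The contradiction is established from the text: sections 2.6 and 3 give opposite orders, and one must be withdrawn. It is more than editorial, because the Discussion counts concealment until baseline among its defences against expectation bias and section 2.6 as written removes that defence.

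The bias is conditional on section 2.6 being followed, and its size is unknown. Under the assumed range (b = 0.1-0.2 SD, ρ = 0.5-0.7, shift confined to baseline, 42 per arm), an adjusted contrast would be off by 0.05-0.14 SD with type I error of about 6-15%, and a change score by 0.1-0.2 SD with type I error of about 7-22%. These figures show what could be at stake and do not estimate what will happen. The concern applies chiefly to BDI-II, GAD-7 and PSS-10. Cognition and blood measures are not self-ratings and are less open to this mechanism.

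Once participants have been enrolled under the section 2.6 order, no pre-disclosure baseline exists and analysis cannot restore one. The Introduction says the article precedes recruitment, so the order can be settled in time.

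**What to change.** State one order in section 2.6 and in the Discussion, and check section 2.7 and Figure 1 against it: consent, eligibility check, all of visit 1 (questionnaires, cognitive tests, blood sample and physical measures), and only then opening of the envelope, disclosure of the arm and arm-specific instructions. Delete the sentence in section 2.6 that places randomisation before baseline.

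If randomisation has to come first for logistical reasons, say so, and withhold both disclosure and arm-specific instructions until visit 1 is complete. The section 2.6 sentence on immediate disclosure and the opening of section 2.7 would then need rewording.

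The cost is a wording amendment with the prior ethics approval that section 2.12.2 already requires. It needs no extra visit, participants or measurements, since the envelope can be opened at the end of visit 1.
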